#### Primary Outcome Measures

##### Depression

Depression is assessed using the PHQ-9 [54]. The PHQ-9 is a brief 9-item depression screening tool based on the symptoms that comprise a diagnosis of major depressive disorder. Scores range from 0-27, with scores between 0-4 indicating minimal depression, 5-9, mild depression; 10-14, moderate depression; 15-19, moderately severe; and ≥20, severe depression. In patients with cardiac conditions, research has demonstrated an optimal PHQ-9 threshold of ≥6 [55,56], which combined improved sensitivity and retained specificity (sensitivity=83% and specificity=76% [56]) as compared to a threshold of ≥10, for detecting major depressive disorder based on a structured clinical interview. The PHQ-9 has been endorsed by the NHFA as the recommended tool for depression screening [57].

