### Data Analysis

In evaluating outcomes, there will be two groups of participants based on the mode of delivery: “self-directed” and “supported.” All statistical analyses will be performed on an intention-to-treat (ITT) basis with *P*<.05. In the case that ITT produces a null finding, it is possible that this is due to participants in the supported group not participating in the additional telephone sessions (that is, not receiving the intended treatment). To test that hypothesis, we will then undertake treatment-received analysis (also called Per Protocol) whereby only those who received the treatment in accordance with the protocol are included. This will enable us to determine whether any differences were obtained between those who received the self-directed treatment and those who received the supported treatment. *P* values less than .05 will be considered significant for the primary outcome and those less than .01 will be considered significant for secondary outcomes. The effect of the intervention on the primary and secondary outcomes at 6 months will be assessed using analysis of covariance (ANCOVA) models that include the baseline value of the outcome as a covariate and the group assignment (self-directed versus supported) as a categorical variable. The treatment effect, its effect size (Hedge g), and 95% CIs for the treatment effect and within-group changes from baseline to 6 months will be calculated from the ANCOVA models. The sensitivity of the results to missing data will be evaluated using a data-based multiple imputation procedure.

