### Primary Outcome Measures: Depression, Physical Activity, and Dietary Intake

As the main outcomes, we will examine differences between the 2 groups in the proportion of participants who are:

classified as *nondepressed* at baseline, post program, and follow-up (based on a PHQ-9 score of <6) [55,56],achieving physical activity guidelines of ≥150 minutes of physical activity per week [52] at baseline, post program, and follow-up, orachieving healthy dietary guidelines of DQT scores >60% [62] at baseline, post program, and follow-up.

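### Baseline PHQ-9, activity and DQT scores are not used to adjust the yes/no main outcomes; adding them to baseline status would give a small, nearly free gain in precision

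*Protocol article*

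**What the plan says.** In the protocol article, Data Analysis sets out a single ANCOVA approach for the 6-month results, primary and secondary alike. It calls for "models that include the baseline value of the outcome as a covariate and the group assignment", and no further covariate is named. The same section asks for Hedges g and within-group changes from this model.

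The section on the primary outcome measures within the analysis plan then makes the main outcomes binary: "we will examine differences between the 2 groups in the proportion of participants who are" non-depressed, sufficiently active or eating healthily. The depression classification is made "at baseline, post program, and follow-up (based on a PHQ-9 score of <6"), and the activity and diet classifications are made at the same three times. The activity criterion is "achieving physical activity guidelines of ≥150 minutes of physical activity per week"; the diet criterion is a DQT score above 60%.

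Each classification comes from a finer measurement. For the PHQ-9, "Scores range from 0-27". The Active Australia Survey supplies weekly minutes, and the DQT has 13 items scored 0 to 10. The Measures section says that all participants complete these instruments at baseline.

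**The concern.** Taken together, the two sections leave the baseline scores out of the analysis of the proportions. If the covariate is baseline status, a participant with a baseline PHQ-9 of 6 and one with 25 get the same covariate value, although their chances of scoring below 6 at follow-up are unlikely to be alike. If the covariate sentence is about scores, the comparison of proportions has no stated adjustment.

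Precision is at stake, not validity. The sample size has no slack and recruitment has closed at 122 participants, so any further precision for these outcomes has to come from the analysis.

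**Working it through.** **1. The plan's own figure.** Inputs from Sample Size and Power: effect size 0.55, power 80%, significance .05 (taken as two-sided), attrition 12%.

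n per arm = 2 × (1.960 + 0.842)² / 0.55² = 51.9, rounded up to 52. Then 52 / 0.88 = 59.1, rounded up to 60 per arm, or 120. The stated figure reproduces and leaves no reserve. Expected completers: 120 × 0.88 = 105.6, about 106 or 53 per arm.

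**2. Model for the gain.** Assumptions, not from the article: baseline and follow-up scores are bivariate normal with correlation r and are cut at the same threshold c, with a share p at target. For a linear model on the risk-difference scale, the variance of the arm difference is proportional to 1 − R², where R² is the share of variance in follow-up status explained by the baseline covariates.

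- Status alone: R² = [(P11 − p²) / (p(1 − p))]², where P11 is the probability of being at target both times.
- Score alone: R² = r² φ(c)² / (p(1 − p)), where φ is the normal density.
- Both: R² = (a² + b² − 2abk) / (1 − k²), where a and b are the correlations of follow-up status with baseline status and score, and k is the correlation between those two.

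**3. Worked case, r = 0.6 and p = 0.65.** P11 = 0.5138 and φ(c) = 0.3704.

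- Status: [(0.5138 − 0.4225) / 0.2275]² = 0.161, so a = 0.401.
- Score: 0.36 × 0.1372 / 0.2275 = 0.217, so b = 0.466.
- k = 0.3704 / √0.2275 = 0.777. Both: R² = 0.221.
- Variance ratio, both against status: (1 − 0.221) / (1 − 0.161) = 0.93. Interval width ratio: √0.93 = 0.96.

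**4. Range.**

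| r | p | R² status | R² both | Variance ratio | Width ratio |
|---|---|---|---|---|---|
| 0.4 | 0.75 | 0.057 | 0.087 | 0.968 | 0.984 |
| 0.4 | 0.50 | 0.069 | 0.102 | 0.964 | 0.982 |
| 0.7 | 0.75 | 0.220 | 0.282 | 0.920 | 0.959 |
| 0.7 | 0.50 | 0.244 | 0.318 | 0.901 | 0.949 |

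Adding the score to status therefore cuts the variance by about 3 to 10% and the width by about 2 to 5%. In participants this is 106 × (1/0.968 − 1) = 3.5 to 106 × (1/0.901 − 1) = 11.6. Against no adjustment, the cut equals R² for both: 0.087 to 0.318, or about 9 to 32%.

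**5. Finite-sample check.** 53 per arm, 4,000 simulated trials per setting, 0.55 SD shift, 50% at target before the shift:

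| r | Half-width, status | Half-width, score + status | Power, status | Power, score + status |
|---|---|---|---|---|
| 0.3 | 0.182 | 0.181 | 61.5% | 62.4% |
| 0.5 | 0.175 | 0.171 | 64.6% | 66.2% |
| 0.7 | 0.163 | 0.156 | 71.4% | 75.9% |

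At r = 0.3 there is next to nothing to gain. With 60% at target and r = 0.3, the two models cannot be told apart (half-width 0.171 for both).

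**6. Skew.** With a log-normal score entered untransformed, the variance ratio for score plus status against status is 0.95 to 0.99. The same skewed score used instead of status gives ratios near 1 and in some settings above 1, so status should stay in the model.

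**The case against.** The strongest objection is that the article nowhere says the covariate is at-target status. Hedges g, within-group changes and a sample size built on a standardised mean difference all suit ANCOVA on scores, where the baseline score already is the covariate. This stands as far as it goes: a reader might infer that the plan knowingly throws the baseline scores away, and the text does not support that. But on the score reading the proportions, which are named as the main outcomes, have no stated covariate, so the scores still do not serve them.

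A second objection is that the functional form of a covariate belongs in the SAP, which is not shown. The transformation alone would indeed be such a detail. The article, however, does fix the model's terms, and the suggestion concerns that stated choice.

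Third, the gain is small. This is correct. Using the best nonlinear predictor of follow-up status, one might quote slightly more (R² of 0.227 in place of 0.221 in the worked case), but that is not what a linear score term delivers.

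Fourth, the gain does not carry over to every model. This is also correct: in logistic regression the interval for the conditional odds ratio need not narrow, although power still rises. A reader might also infer that adjusting for status alone is biased or invalid; it is neither.

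**Conclusion.** The point holds as an optional improvement. On either reading of Data Analysis, the baseline PHQ-9 score, weekly minutes and DQT score are unused for the yes/no main outcomes. Using them with baseline status would make the risk-difference interval about 2 to 5% narrower than status alone, if the correlation is 0.4 to 0.7 and 50 to 75% are at target. Neither quantity is in the article, and weaker correlations give less.

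The point is also secondary to a larger question: whether scores or classifications are primary. In the same simulations, with 40 to 60% at target and correlations of 0.3 to 0.7, power for the yes/no outcome with baseline adjustment was about 58 to 78%, against about 83 to 98% for ANCOVA on the score. If the primary analysis is settled as scores, this point falls away for it and remains only for the proportions.

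**What to change.** For each yes/no main outcome, state before outcomes are compared by arm that the model contains group, baseline at-target status and the baseline score on the same instrument. Fix the scale in advance rather than after looking at the data, for example square root of PHQ-9, log(minutes + 1) and untransformed DQT. Report the standardised risk difference with its 95% CI. Make clear in the same sentence whether the ANCOVA and Hedges g apply to scores, to proportions or to both.

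The cost is a change of wording and one extra model term, one degree of freedom in about 106 completers. No new data are needed.

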### Recruitment and Participants

A total of 120 participants will be recruited into the trial, with 60 randomly allocated to each of the 2 arms of the trial. Participants will be adults (over 18 years of age) who have had an acute cardiac event, such as AMI, coronary artery bypass graft surgery (CABGS), or percutaneous coronary intervention (PCI), in the past 12 months. Participants are required to be fluent in English to comprehend the *Back on Track* program, which is currently available in English only. Participants are also required to have access to the internet and a computer or tablet.

Participants are being recruited using both direct engagement via a nationwide social media recruitment drive, and indirect engagement via cardiac health professionals and community-based cardiac support organizations, namely HeartBeat Victoria and Heart Support Australia. A promotional flyer is used for all promotion and recruitment. The nationwide social media recruitment drive involves announcements about the trial on internet-based social media platforms such as Facebook, Twitter, and LinkedIn. HeartBeat Victoria and Heart Support Australia also promote the study to their members, who are all people living with heart disease. Details of eligibility criteria are provided on the relevant websites and organization promotional material. Likewise, the trial is being promoted among cardiac health professionals, based on a list of health professionals who are involved in cardiac rehabilitation services across Australia or have attended past ACCH training programs.

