In all cases of recruitment, both direct and indirect, potential participants are directed to the ACHH website for detailed information about the study and for instructions on how to register on the internet. Screening for eligibility is undertaken at the time of participant registration via the ACHH website using a set of brief screening questions; specifically, participants are asked to provide their name and contact details, type, and date of cardiac event and to confirm that they are able to read and understand English and that they have access to the internet and a computer or tablet device. All participants are asked to read, sign, and return the participant information and consent form (PICF) after registration and prior to randomization and being given program access. The PICF is emailed to participants via the secure web-based data management and survey program, Research Electronic Data Capture (REDCap), which they sign and return electronically to ACHH.

Once registered, participants are randomly allocated to either the self-directed or the supported arm of the trial using an independent and automatic random allocation numbering system. The person undertaking the random allocation is blind to group and participant details. All participants are then asked to complete the web-based baseline questionnaire, also disseminated using REDCap. The link to questionnaires is emailed to participants at each timepoint. Access to the *Back on Track* program is granted to participants for a 2-month period after they complete the baseline questionnaire.

Participants are asked to recomplete the main outcome measures again post program (2 months after initial access to the program) and at 4-month follow-up (6 months after program access). Again, the REDCap survey link is emailed to participants.

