##### Physical Activity and Sitting Time

Physical activity and sitting time are measured using the Active Australia Survey (AAS) [58] with sitting questions from the International Physical Activity Questionnaire (IPAQ) (long form) [59]. The 8-item AAS measures frequency of walking, moderate activity, and vigorous activity in the last 2 weeks. The AAS has acceptable reliability and validity in the Australian community [60] and CR populations [61]. Participants are classified, according to the NHFA, as achieving the recommended target for adequate physical activity for secondary prevention [52] if they have been engaged in ≥150 minutes of physical activity per week combined across the 3 domains assessed. Sitting time is measured using the relevant questions from the IPAQ long form which asks participants about their total time spent sitting on a typical weekday and weekend day [59].

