##### Additional Measures

Basic sociodemographic (namely age, sex, country of birth, marital status, living arrangement, employment status, educational level, and financial strain), medical (other physical and mental health conditions), and event-related information (event type, date of event, and attendance at cardiac rehabilitation) is collected via a self-report questionnaire, using standard questions used in previous ACHH studies [74].

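### The between-arm model leaves out time since the cardiac event, which is known before randomization; this costs some precision and protection against chance imbalance, but causes no bias

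*Protocol article*

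**What the plan says.** - **Entry window** (Recruitment and Participants): an acute event such as infarction, bypass surgery "or percutaneous coronary intervention (PCI), in the past 12 months". No minimum interval is given.
- **Event date** (same section): at registration, before allocation, "participants are asked to provide their name and contact details, type, and date of cardiac event".
- **Rehabilitation attendance** (Additional Measures): "event-related information (event type, date of event, and attendance at cardiac rehabilitation) is collected via a self-report questionnaire". The Measures section places sociodemographic items at baseline only, and I take these items to be in the same questionnaire.
- **Order of steps** (Recruitment and Participants): random allocation comes first. "All participants are then asked to complete the web-based baseline questionnaire", and program access follows.
- **Activity measure** (Physical Activity and Sitting Time): the survey "measures frequency of walking, moderate activity, and vigorous activity in the last 2 weeks".
- **Model** (Data Analysis): the ANCOVA models "include the baseline value of the outcome as a covariate and the group assignment (self-directed versus supported) as a categorical variable". The article gives event date and rehabilitation attendance no role in allocation or in any analysis.
- **Primary outcomes** (Primary Outcome Measures, in the analysis part): the proportions nondepressed, meeting the activity guideline and meeting the diet guideline.

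**The concern.** A two-week recall shortly after surgery may describe convalescence, while the same recall at eleven months describes settled habit. Two participants with the same low baseline activity could therefore have quite different expected values six months later, and the baseline score alone does not tell them apart. Rehabilitation attendance raises a similar issue. The Introduction says that rehabilitation improves health outcomes and that only about 30% of eligible people attend, so the sample is probably mixed.

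If these variables predict the 6-month outcome beyond the baseline score, leaving them out puts explainable variation into the error term. It also leaves the estimate more exposed to a chance difference between arms of about 53 completers each. Both variables are already collected, and event date is known before randomization, so the loss is avoidable.

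**Working it through.** **Inputs from the article (Sample Size and Power).** Standardized effect 0.55, power 80%, alpha .05 (two-sided assumed), 60 per arm, 12% attrition.

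**Input not in the article.** R², the share of residual variance explained by the added covariates beyond baseline and arm. The range used is 0.02 to 0.10, with 0 as the unfavorable case.

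**1. The plan's own figure.** n per arm = 2(1.960 + 0.842)² / 0.55² = 51.9, so 52. Dividing by 0.88 gives 59.1, so 60 per arm and 120 in total. The stated sample size reproduces and does not depend on the covariates discussed here.

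**2. Precision in a continuous-outcome ANCOVA.** The standard error is multiplied by √(1 − R²). Power at 52 per arm is Φ(0.55 / [√(1 − R²) × √(2/52)] − 1.96).

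| R² (assumed) | SE reduction | Power |
|---|---|---|
| 0 | 0% | 80.1% |
| 0.02 | 1.0% | 80.9% |
| 0.05 | 2.5% | 82.1% |
| 0.10 | 5.1% | 84.0% |

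The equivalent gain in sample size, R²/(1 − R²), is 2%, 5% and 11% for the last three rows.

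**3. Chance imbalance.** Completers per arm: 60 × 0.88 = 52.8, about 53. The arm difference in mean time since event has SD √(2/53) = 0.194 in SD units. The chance of a difference above 0.2 SD in either direction is 30%, and above 0.3 SD it is 12%.

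An imbalance moves the estimate by imbalance × √R². With √R² = 0.14 to 0.32:
- 0.2 SD moves it by 0.03 to 0.06 residual SD;
- 0.3 SD moves it by 0.04 to 0.09 residual SD.

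The planned effect is 0.55.

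**4. Is the stated model biased?** A simulation used 5,000 trials per setting and 52 per arm. Time since event was uniform over 0 to 12 months and rehabilitation attendance was 30%. In the settings where the covariates mattered, the baseline–outcome slope varied with time since event. Prognostic strengths were assumed.

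| Prognostic strength | Type I error, stated model | Power, stated model | Power, with both covariates |
|---|---|---|---|
| None | 4.8% | 89.1% | 88.3% |
| Moderate | 4.5% | 84.8% | 87.7% |
| Strong | 4.9% | 70.8% | 83.7% |

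The mean estimate was 0.00 under the null and 0.55 under the alternative in every setting, with or without the covariates. The difference is in precision only. The cost when the covariates are uninformative is 0.8 points.

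**5. Scope.** Steps 2 and 3 hold for a linear model. The primary outcomes are proportions. In a logistic model, adding a prognostic covariate changes the odds ratio being estimated, so the SE formula does not carry over.

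**The case against.** The strongest reply is that nothing here is wrong. ANCOVA on baseline and arm is valid under random allocation, random imbalance is already reflected in the interval and P value, and further covariates may be set in an analysis plan that is not shown. The benefit rests on an R² for which the article has no figure. All of this stands, and it limits the point to efficiency and robustness. It does not remove the point: the article states the content of its model, and a better one is available from data already in hand.

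A reader might infer more than the document supports:

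- **That the treatment effect is biased, or that an imbalance carries over in full.** It enters only in proportion to the covariate's remaining prognostic strength, and it averages to zero over randomizations.
- **That spontaneous recovery or rehabilitation outweighs the effect of two telephone sessions.** The article has no data on outcomes by time since event.
- **That allocation was unstratified.** A condensed article is merely silent on this.

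Two objections concern the remedy, and both are right. Rehabilitation attendance is self-reported after allocation, and a negative answer can mean not yet or never. Also, a main effect of time does not model a baseline slope that changes with time. In the simulation, however, the main effect recovered precision without bias even though the slope did vary.

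**Conclusion.** The point holds as a modest improvement to a stated model. The between-arm analysis as written is unbiased and keeps its type I error. It gives up an assumed 1% to 5% of the standard error in a continuous-outcome ANCOVA, or roughly 1 to 4 points of power at 52 per arm. It also leaves chance imbalances worth about 0.03 to 0.09 residual SD uncorrected. These sizes rest on an assumed R² of 0.02 to 0.10. If the true value is near zero, adjustment costs under one point of power. For the binary primary outcomes the size of the gain has not been quantified.

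Time since event has the better claim, because it is fixed and known before allocation. Rehabilitation attendance is secondary.

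Adjustment would not help with a neighboring problem. Under Data Analysis, "within-group changes from baseline to 6 months will be calculated from the ANCOVA models", and no arm is untreated, so recovery after the event could look like program benefit. These covariates cannot separate the two, nor do they account for rehabilitation attended during follow-up.

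**What to change.** In Data Analysis, before any between-arm results are seen:

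1. Add time from event to enrollment as a covariate in each primary between-arm model. Use the event date given at registration and state the functional form, for example log weeks, including how events less than a week old are handled.
2. Optionally add rehabilitation attendance (yes/no), limited to attendance before enrollment.
3. For the three primary proportions, use the same covariates in a binary-outcome model and report a marginal (standardized) risk difference with its 95% CI, so that the effect being estimated does not change with adjustment.
4. Keep the model with baseline and arm only as a sensitivity analysis.

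The cost is one or two degrees of freedom per model, a few lines of specification and no new data.

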### Objectives

The aim of this study is to assess the benefits, in terms of behavioral and emotional well-being, of the web-based *Back on Track* self-management program, and to test whether participants obtain enhanced benefit through the provision of one-on-one telephone support from a trained lifestyle counselor (supported arm), over and above benefit obtained through completing the web-based program alone (self-directed arm). By including 2 follow-up assessments, one on postprogram completion (2 months) and one at 4 months post program (6 months postenrollment), we aim to assess both immediate and sustained benefits.

We hypothesize that participants randomly allocated to each arm of the trial will show significant improvement in their behavioral and emotional well-being, self-efficacy, and self-rated health from the preprogram to postprogram assessments, with benefits sustained 4 months after program completion. We also hypothesize that participants allocated to the supported program will demonstrate superior improvements in behavioral and emotional well-being, self-efficacy, and self-rated health compared to those allocated to the self-directed arm, at both the postprogram and follow-up assessments.

Ethical approval was granted by the Deakin University Human Research Ethics Committee (2019-438). This project has been funded by the HCF Research Foundation. This study will be conducted and reported in accordance with the CONSORT-EHEALTH guidelines [50].

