### Sample Size and Power

Our sample size is based on a systematic review of telehealth-based cardiac rehabilitation [28] on lifestyle behaviors, health outcomes, and quality of life, where the effect sizes on promoting healthy lifestyle ranged from 0.42 to 1.29. Taking a conservative approach, we expect a medium effect size of 0.55. Allowing for 80% power and a significance threshold of .05, the estimated sample size is 120 (60 per arm), which takes into consideration an expected attrition rate of 12% based on prior studies with similar posttest time points of 2-4 months [31,51].

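### The 95% CIs for within-arm change are taken from the baseline-adjusted ANCOVA, whose standard errors omit the sampling error of the baseline mean, so they are modestly too narrow for the population mean change

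*Protocol article*

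**What the plan says.** Under Data Analysis, the protocol article assesses the 6-month outcomes with ANCOVA models that "include the baseline value of the outcome as a covariate and the group assignment (self-directed versus supported) as a categorical variable". It then says that the 95% intervals for the treatment effect and "within-group changes from baseline to 6 months will be calculated from the ANCOVA models". The same model therefore supplies both the between-arm and the within-arm intervals.

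Under Objectives, the first hypothesis is that "participants randomly allocated to each arm of the trial will show significant improvement in their behavioral and emotional well-being" between the pre- and postprogram assessments, with the benefit still present 4 months after the program ends. Under Study Design, both arms receive the web-based program and differ only in the telephone sessions. The later section on change over time in psychosocial and attitudinal measures plans a repeated-measures analysis of variance, but to compare the two groups. No other within-arm interval is described.

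**The concern.** An ANCOVA takes the baseline values as fixed. For the difference between arms this does no harm, because the baseline mean cancels. For a change within one arm it does not cancel. The change is the adjusted 6-month mean minus a baseline mean, and that baseline mean is estimated from the same sample. If the interval is read straight from ANCOVA output, this source of error is missing whenever the regression slope differs from 1.

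With no arm that goes without the program, evidence that each arm improves has to come from within-arm change. Intervals that are too narrow would declare improvement somewhat more often than the nominal 5% when there is none.

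**Working it through.** **Inputs from the protocol article (Sample Size and Power).** Effect size: "we expect a medium effect size of 0.55". Error rates: "Allowing for 80% power and a significance threshold of .05". Sidedness is not stated; two-sided is used here. Attrition is 12%, and the target is 120 participants, 60 per arm.

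**The plan's own figure.** 2 × (1.96 + 0.8416)² / 0.55² = 51.9, so 52 per arm. Then 52 / 0.88 = 59.1, rounded up to 60 per arm, or 120 in total. The t-based version gives 52.87 / 0.88 = 60.1. The stated figure reproduces. It serves here only to fix the number analysed: 60 × 0.88 = 52.8, about n = 53 per arm.

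**Assumptions.** The baseline/6-month correlation r is not in the article, so 0.3, 0.5, 0.7 and 0.9 are tried. The SD is set to 1 at both times, so the slope equals r.

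**Variances per arm.**
- ANCOVA output, baselines fixed: (1 − r²)/n.
- Full variance, change from the overall baseline mean (2n people): (1 − r²)/n + (1 − r)²/(2n).
- Full variance, change from the arm's own baseline mean: (1 − r²)/n + (1 − r)²/n = 2(1 − r)/n.

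Actual coverage of the nominal 95% interval is 2Φ(1.96 × ratio) − 1, where ratio is the ANCOVA SE divided by the full SE.

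**Worked case, r = 0.5.** ANCOVA variance: 0.75/53 = 0.01415, SE 0.1190. Overall mean: add 0.25/106 = 0.00236 to get 0.01651, SE 0.1285, ratio 0.926, coverage 93.0%. Own mean: 2 × 0.5/53 = 0.01887, SE 0.1374, ratio 0.866, coverage 91.0%.

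**All cases** (simulated: 20,000 trials for each r, 53 per arm, no true change):

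| r | SE ratio, overall mean | Coverage, formula / simulated | SE ratio, own mean | Coverage, formula / simulated |
|---|---|---|---|---|
| 0.3 | 0.89 | 91.8% / 92.0% | 0.81 | 88.6% / 88.6% |
| 0.5 | 0.93 | 93.0% / 93.0% | 0.87 | 91.0% / 90.8% |
| 0.7 | 0.96 | 94.0% / 93.9% | 0.92 | 92.9% / 93.0% |
| 0.9 | 0.99 | 94.7% / 94.7% | 0.97 | 94.4% / 94.5% |

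The primary outcomes are proportions, so the simulation was repeated with 0/1 outcomes (each split at the median of a latent normal score). At latent correlations 0.5 and 0.7, coverage was 92.1% and 93.3% against the overall mean, and 88.6% and 91.4% against the arm's own mean.

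**Check of the remedies.** For continuous scores, adding the baseline-mean term to the ANCOVA variance, or using a paired interval within the arm, gave simulated coverage of 94.9% to 95.1%.

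**The case against.** The strongest reply is that the article does not say how the standard error of the within-arm change is obtained, or which baseline mean is subtracted, and that a condensed article may leave this to a fuller plan. That limits what can be claimed. A reader might infer that the plan states that the baseline mean is treated as known; it does not. It does name the model, and standard output from that model omits the term. The choice of model is therefore a fair target, while the exact SE remains an inference.

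Second, a reader might infer that these intervals are the formal test of the first hypothesis. The article does not say so. The clause that each arm "will show significant improvement in their behavioral and emotional well-being, self-efficacy, and self-rated health from the preprogram to postprogram assessments" concerns the 2-month change, whereas the intervals run from baseline to 6 months. They bear only on the part about sustained benefit. It remains true that no other within-arm interval is described.

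Third, a reader might quote a type I error of 11%. That figure (100% − 88.6% = 11.4%) needs both the arm's own baseline mean and r = 0.3. Adjusted means are ordinarily evaluated at the overall baseline mean, where the error is about 5% to 8% over the range of r. Secondary outcomes are also judged at .01, so 5% is not the benchmark for all measures.

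Fourth, conditional on the observed baselines the interval is valid. This stands, but a hypothesis about improvement in cardiac patients is more naturally about the population than about the baselines that happened to be drawn. Part of the ANCOVA interval's advantage over a paired one is also legitimate, because it borrows baseline data from the other arm.

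**Conclusion.** The point holds in a modest form. Read from standard ANCOVA output, the 95% CIs for within-arm change to 6 months are too narrow for the population mean change. Against the overall baseline mean, the SE is about 11%, 7%, 4% and 1% too small at r = 0.3, 0.5, 0.7 and 0.9, with coverage of about 92% to 94.7%. Against the arm's own mean, coverage falls to about 89% at r = 0.3. At r = 0.9 the shortfall is negligible either way.

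These sizes rest on about 53 per arm, equal variances at the two times, an assumed r, and SEs taken from the model without correction. The between-arm effect and its CI, which are the randomized comparison, are not affected. The point is worth correcting because both arms receive the program and the correction is cheap; it does not undermine the trial's main comparison.

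**What to change.** Keep the ANCOVA for the between-arm effect and its CI. For within-arm changes and their 95% CIs, state one of these:

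- a paired analysis within each arm (for the binary primary outcomes, a paired difference in proportions);
- a repeated-measures model with baseline as a response: linear for scores, a binary-outcome equivalent for proportions. With all three assessments as responses, it also covers the 2-month change in the first hypothesis;
- the ANCOVA-based change with the baseline-mean variance term, (1 − slope)² × baseline variance / number contributing to the baseline mean, added to the squared SE.

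The cost is one sentence of analysis wording and no new data. The within-arm intervals become slightly wider. The simple paired version is somewhat less precise than the corrected ANCOVA or model-based one: at r = 0.5 its SE is 0.1374 against 0.1285, about 7% larger.
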